### Blinding

The trial will be triple-blinded (participant, healthcare provider, and statistician). The placebo has the same appearance, volume, weight, odour, and taste as the active product. There will be unblinding of the individual participant’s randomized N-of-1 sequence for the healthcare provider and participant only upon receiving individual trial reports or on participant request to stop the trial early.

### Cointerventions

All participants will be encouraged to continue practicing good sleep hygiene consistently throughout their N-of-1 trial. Participants will receive other medications and healthcare tests their primary physician deems appropriate. If a child is already on the following medications, we will require stable doses of each: approved anti-depressants, anxiolytics, sedatives/hypnotics, and clonidine throughout the 6-week trial. If not already taking these medications, the child may not start them regularly during the trial. It is preferable that participants abstain from coffee, alcohol, and high caffeine energy drinks for 1 week prior to the sleep-hygiene phase, during the sleep-hygiene phase, and during the trial itself. Any caffeine intake during the previous week will be recorded during the sleep hygiene phase, at baseline, and at the end of each week during the trial.

Any changes in dose/frequency/type of stimulant treatment for ADHD and whether the patient is taking nontrial melatonin will be recorded throughout the trial.

### Contamination

Because melatonin is readily available over the counter in Canada, contamination (parents providing melatonin to their child) could potentially pose a risk. The use of N-of-1 trials is expected to prevent this from occurring, as parents are guaranteed that their child will receive melatonin during the course of the trial. To further reduce contamination, parents will be reminded that their child will be on active therapy in a blinded fashion, and they would not want to “double dose” their child. Physician information letters will be sent to the child’s doctor to remind them not to recommend melatonin during the study.

### Sample size

A proposed sample size was calculated for the parallel group RCT. The null hypothesis is that both group means are equal, and the alternative hypothesis is SOL will be 42 minutes on melatonin and 72 minutes on placebo [22]. To account for a potential dropout of 25 %, we assume that 25 % of the participants will show no effect of treatment and will therefore have a SOL of 72 minutes under both treatments. The average time in the treatment group will then be 49.5 minutes (as ¾ will have a time of 42, and ¼ a time of 72). The intent-to-treat effect will then be a 22.5-minute reduction in SOL. Assuming a pooled standard deviation of 60 minutes [22], randomization of 150 patients per group (300 total) will provide 90 % power with a type I error rate of 0.05 using a two-sided test. We will need to recruit 177 patients per group (354 total) to commence the sleep-hygiene phase in order to account for the 15 % of individuals expected to respond to sleep hygiene. Because the N-of-1 design will use multiple crossovers for each patient, this sample size will also achieve sufficient power for the aggregated N-of-1 analysis.

### Proposed trial outcome measures

#### Primary outcomes

SOL (in minutes) will be measured daily by sleep diaries completed by parents. Participants who are > 12 years will assist in filling out sleep diaries. Sleep dairies are among the most common assessment tools in sleep research [28, 42].

#### Secondary outcomes

In a subgroup of children, SOL (minutes) will also be measured daily by actigraphy, which are validated to measure sleep quality in clinical research [43]. We will use Actiwatch Spectrum (Phillips Respironics, Murrysville, PA, USA). The mean amount of time awake at night (minutes) and mean duration of sleep while in bed (minutes) will be measured daily by sleep diaries and actigraphy. The number of awakenings after sleep onset will be measured by sleep diaries. Sleep efficiency (proportion of time spent asleep while in bed) will be measured daily by actigraphs. Daytime behavior, specifically core ADHD symptoms, will be measured weekly by the Conners’ 3 Parent Short form [44]. The quality of life of the participants will be measured weekly by the Pediatric Quality of Life Inventory-32 [45]. The parent’s quality of life and fatigue will be measured weekly by the SF12-v2 [46]. See Table 1 for a list of outcome measures used in this study.

**Table 1 Tab1:** List of outcome measures used

Outcome	Tool	Frequency of measurement
SOL	Sleep diary	Daily
	Actigraphy	
Amount of time awake at night	Sleep diary	Daily
	Actigraphy	
Number of awakenings after sleep onset	Sleep diary	Daily
Sleep efficiency	Actigraphy	Daily
ADHD Symptoms	Conners’ 3 Parent Short form	Weekly
Participant quality of life	Pediatric Quality of Life Inventory-32	Weekly
Parent quality of life and fatigue	SF12-v2	Weekly
Adverse events	Clinical trial adverse event form	Daily

#### Adverse events

Each participant will receive ongoing safety monitoring throughout the trial. Parents will be asked about side effects during weekly telephone follow-ups. All adverse events will be forwarded to the DSMB. The DSMB consists of three members with clinical, methodological, and NHP expertise who are independent of the trial. The DSMB will review all documented harms during the study and adjudicate them with regards to causality. Frequency and severity of any adverse events will be reported using the Clinical Trial Adverse Event form that includes open-ended questions on potential adverse reactions. Health Canada and Therapeutic Goods Australia will be informed of all serious adverse events (those warranting hospitalization) within 7 days.

### Withdrawal

If participants experience intolerable adverse events, they may choose to withdraw, or the investigators may make this decision in the best interest of the patient. Patients who are lost to follow-up, who cannot be contacted for telephone follow-ups, or who wish to discontinue medication for 7 or more consecutive days will be withdrawn. If a participant chooses to withdraw, a withdrawal report form will be completed. Assessments and reason(s) for withdrawal will be recorded.

### Early stopping (within a treatment period)

While pre-specifying the number of paired periods in an N-of-1 trial strengthens statistical analysis of the data [47], N-of-1 trials may accommodate early stopping within a treatment period. Early stopping most commonly occurs for three reasons—perceived lack of effectiveness, a dramatic improvement in the target outcome or safety concerns. If a participant/parent feels strongly that a period should be stopped early, the research nurse will give them the option of switching to the next period’s medication after day 4 of that period, rather than withdrawing from the trial. Early stopping does not compromise the validity of the data acquired as all decisions are made with the blind intact, and the randomization sequence unaltered. Early stopping within a treatment period (i.e., early progression to the next treatment period) promotes trial completion, as opposed to withdrawal, as participants recognize that we will try to accommodate their requests within the confines of the study.

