## Methods/design

### Study design

We will conduct a prospectively planned, head-to-head comparison of a parallel-group RCT design with aggregated N-of-1 trial data. The trial is a multicenter, randomized, triple-blind, placebo-controlled series of N-of-1 trials with an embedded RCT. Half the participants will be randomly allocated to melatonin in the first period; the other half will start with placebo; and the RCT will include the data from the first period only. For the N-of-1 trial, each participant will undergo three pairs of treatment/placebo periods (each period is 1 week long, and each N-of-1 trial will last a total of 6 weeks). See Fig. 1 for scheme of the study design, Fig. 2 for flow of participants through study, and the SPIRIT checklist (Additional file 1).

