### Melatonin

Previous research suggests that an oral dose of 2.5–10 mg before or at the desired bedtime is well tolerated in children [41]. Similar to previous pediatric trials [40], we will use weight-based dosing, giving 3 mg of sublingual melatonin to those children who are < 40 kg and 6 mg to those ≥ 40 kg. Melatonin will be taken once daily, 30 minutes prior to bedtime. Placebo with an identical appearance has been manufactured. The clinical effect of melatonin is rapidly evident, and melatonin has a short half-life (0.54–2 h). Therefore, an appropriate duration of each treatment period is 1 week. Data from day 1 of each period will be discarded to provide a washout period. If a carryover effect is found subsequent to day 1, appropriate adjustments will be made, e.g., discarding an extra day’s data.

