#### Parallel-group RCT analysis

Using data from the first treatment period, we will compare those who received melatonin with those who received placebo based on intent-to-treat for all outcomes adjusted for the average baseline SOL determined by the pre-randomization sleep-hygiene phase. Outcomes measured daily will be analyzed both with time series methods and by using the outcome averaged across the treatment period. Outcomes measured weekly provide only one measurement per participant. Secondary analyses will examine effects defining treatment as that actually received.

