#### Analysis of individual N-of-1 trials

At the end of each participant’s N-of-1 trial, a patient report will be forwarded to the referring physician in order to guide treatment decision. The patient report will present (1) the child’s SOL (according to parent diaries) for each day of the study; (2) the child’s mean and median SOL on both treatments; (3) whether the child’s SOL has normalized below 30 minutes; (4) whether the SOL is within the parent’s expectations of significant improvement; and (5) any reported adverse events. The patient and physician will make an individual decision about the continued use of melatonin.

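### Blinding does not stop outcome-driven early switching from biasing the unweighted period average of sleep onset latency, most likely in favour of melatonin if it works

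*Protocol article*

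**What the plan says.** The section on early stopping within a treatment period offers families who feel strongly "the option of switching to the next period’s medication after day 4 of that period, rather than withdrawing from the trial". It gives the usual reasons as "perceived lack of effectiveness, a dramatic improvement in the target outcome or safety concerns". It then states that "Early stopping does not compromise the validity of the data acquired as all decisions are made with the blind intact", adding that the randomization sequence is unaltered.

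Four other parts of the protocol article determine what a shortened period contributes:

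- Study design: "each period is 1 week long, and each N-of-1 trial will last a total of 6 weeks".
- Interventions, Melatonin: "Data from day 1 of each period will be discarded to provide a washout period".
- Parallel-group RCT analysis: "Outcomes measured daily will be analyzed both with time series methods and by using the outcome averaged across the treatment period". The section adjusts for average baseline SOL and ranks neither of the two analyses above the other.
- Analysis of individual N-of-1 trials: the report to the physician gives "the child’s mean and median SOL on both treatments".

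The aggregated analysis is a multilevel random-effects model and is not described as an analysis of period averages. The missing-data section addresses the aggregated analysis only. No section says how a shortened period is weighted in an average.

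**The concern.** Blinding prevents knowledge of the treatment from driving a switch. It does not prevent the SOL values themselves from driving it, and too little effect and dramatic improvement are both judgements about those values. If a run of bad nights triggers the switch, the later nights, which would on average have drifted back toward the child's usual level, never occur, and the high average is frozen. A run of good nights freezes a low one. An unweighted period average then counts three selected nights as heavily as six unselected ones.

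If melatonin works, placebo periods are more likely to be cut on bad runs and melatonin periods on good runs, so the two errors tend to add. SOL is the primary outcome, so this affects the size of the effect reported. It also bears on the second primary objective, which asks whether N-of-1 trials and the parallel-group RCT give similar estimates. Period averages in one and nightly data in the other could create a gap of a few minutes that comes from truncation alone.

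**Working it through.** **The plan's own figure.** The Sample size section uses a difference of 22.5 min (0.75 × 42 + 0.25 × 72 = 49.5, against 72), SD 60, two-sided 0.05 and 90% power. n = 2 × (1.960 + 1.282)² × 60² / 22.5² ≈ 149.4, so 150 per group, as stated (power 0.901). The protocol gives no figure for bias from early switching, so the rest is derived.

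**Inputs from the protocol.** Mean SOL is 72 min on placebo and 42 min on melatonin, or 49.5 min after dilution. A full period gives nights 2-7 (six nights). A period cut after day 4 gives nights 2-4 (three nights).

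**Assumptions, not in the protocol.** Nightly within-child SD s of 20, 30 or 40 min; independent nights; a lack-of-effect cut-off cU and a dramatic-improvement cut-off cL, judged against the child's own usual level; a share p of eligible families who switch.

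**Formula.** Let A be the mean of nights 2-4 and C the mean of nights 5-7. A full period contributes (A + C)/2 and a cut one contributes A, so cutting adds (A − C)/2. Given A, this has expectation (A − μ)/2. Averaging over A > cU or A < cL shifts an arm's mean by

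shift = p × ½ × (s²/3) × [f(cU) − f(cL)],

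where f is the normal density with mean μ and SD s/√3. The bias in the difference is the placebo shift minus the melatonin shift.

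**Worked case** (s = 30, cU = 72, cL = 30, p = 1, true 22.5). Here ½ × 300 = 150 and s/√3 = 17.32.

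- Placebo, μ = 72: 150 × (0.02303 − 0.00122) = +3.27.
- Melatonin, μ = 49.5: 150 × (0.00991 − 0.01222) = −0.35.
- Bias: 3.27 + 0.35 = +3.62 min.

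**Results for the unweighted average, in min**

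| Rule | Uptake | True 22.5 | True 30 |
|---|---|---|---|
| 72 / 30 | all | +2.5 to +4.1 | +3.6 to +5.8 |
| 72 / 30 | 20% | +0.5 to +0.8 | +0.7 to +1.2 |
| 90 / 30 | all | +1.2 to +4.8 | +2.0 to +6.0 |
| 60 / 30 | all | +0.4 to +2.2 | +2.0 to +3.8 |
| 45 / 30 | all | −1.4 to +0.2 | −0.7 to +0.9 |
| 45, lack of effect only | all | −2.0 to −2.3 | −2.1 to −2.4 |

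Each range runs over s = 20, 30 and 40. If the 72 and 30 min cut-offs are applied to raw SOL across children whose SD is 60, the bias is only +0.1 to +0.6 min. With no true effect the two shifts cancel, and the simulated type I error is 0.050. With 150 per group, s = 30, the 72/30 rule and a true 22.5, the rejection rate is 0.958 against 0.899 with full periods.

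**Does the planned baseline adjustment cure it?** Not for the unweighted average. With 14 baseline nights, between-child SD 50 and full uptake at 72/30:

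- Unweighted average with baseline adjustment: a true 22.5 is estimated at 25.1 to 26.5 and a true 30 at 33.6 to 35.8.
- Night-weighted model with baseline adjustment: 23.1 to 23.3 and 30.7 to 31.2.
- Nights 2-4 of every period: bias about 0.

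The small residue in the second line arises because families are assumed to judge against the child's true usual level, which the model sees only through the baseline average. When they judge against the recorded baseline itself, a variance-weighted, baseline-adjusted likelihood estimate returns 29.9 to 30.1 for a true 30.

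**Aggregated data** (s = 30, full uptake). A true 22.5 is estimated at 26.2 by unweighted averages and 23.0 by a night-level model with child effects. A true 30 is estimated at 35.3 and 30.8.

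**The case against.** The strongest defence is that the plan already contains the better analyses. The RCT section lists time-series methods beside the average and adjusts for baseline SOL. The aggregated analysis is a multilevel model. Ranking two analyses is often left to an analysis plan that is not shown. This stands in part: the aggregated model, if fitted to nightly data, is largely protected, and silence on ranking alone would not be a point. But the validity claim is a positive statement in the text, and its reason does not support it.

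A second defence is that the size is driven by assumptions. This also stands. The option is for families who feel strongly, some switches will be for safety and unrelated to SOL, and at 20% uptake the bias is about 1 min or less. Against the RCT's unadjusted standard error of 60 × √(2/150) = 6.9 min, even 5.8 min is under one standard error.

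A third is that the alternative to switching is often withdrawal, which would lose later periods as well. That may justify offering the option, but it does not make the shortened average unbiased.

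A reader might go further and infer that the aggregated N-of-1 estimate is off by several of its own small standard errors. The document does not support this, because it does not plan period averages for that analysis. Nor does it support reading the exaggeration as certain: the direction depends on where families set their cut-offs. The reversing case is extreme, though. A 45-min lack-of-effect cut-off with full uptake would end 88% to 99% of placebo periods early.

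**Conclusion.** The point holds in limited form. Blinding does not make outcome-driven shortening of a period harmless, and the statement that validity is not compromised is wrong for the unweighted period average in the RCT. The raw means in the individual reports are open to the same effect, to an extent that depends on whether nights or period means are pooled, which is not stated.

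If melatonin works and families respond to clearly bad or clearly good runs, the likely direction is in its favour, by roughly 0.5 to 6 min on a true 22.5 to 30 min. That range rests on assumed cut-offs, uptake and nightly SD. The bias is under 1 min if families judge raw SOL, is zero under no effect, and can reverse with a low lack-of-effect cut-off. It might be inferred that the RCT's test of no effect is invalid, but the type I error is unaffected in these calculations. What is at risk is the size of the estimate and its comparison with the N-of-1 result. The change should be made, since it costs little and the better analysis is already planned.

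**What to change.** 1. Withdraw the statement that early stopping leaves validity uncompromised. Say instead that blinding and the fixed sequence protect against treatment-driven switching but not against outcome-driven switching.
2. For SOL in the RCT, make the night-level model with baseline average SOL primary and the unweighted period average supportive. State that the aggregated multilevel model is fitted to nightly data.
3. Add a sensitivity analysis using nights 2-4 of every period, all observed before a switch is allowed.
4. Alongside these, report switch rates and reasons by treatment.

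The cost is a few sentences and one extra analysis, with some loss of precision in the nights 2-4 run because it uses three nights of six. That run estimates the effect over those nights, so it should be read beside the primary model and not in place of it. The switching option itself is unchanged.

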### Statistical analysis plan

We will undertake (1) a standard parallel-group RCT analysis comparing results from the first period for treatment and control groups; (2) analysis of individual N-of-1 trials; and (3) aggregated analysis across N-of-1 studies using data from all periods in all participants. Each analysis will report an estimate of the mean difference between treatment groups across the measurements taken over the course of the trial together with 95 % probability intervals and a probability estimate of the likelihood of a treatment effect. Primary analyses will use the Bayesian method with noninformative prior distributions. We will also carry out analyses based on reasonable weakly informative priors and on the likelihood alone as a check on sensitivity to assumptions about the prior distribution. Data on randomized patients at baseline will be summarized with descriptive statistics (mean, median, standard deviation, and ranges) for quantitative variables, and counts and percentages for categorical variables. Regression adjustments will be carried out for variables found to be unbalanced at baseline between treatment and placebo groups. A variety of interaction tests will be carried out to test for subgroup differences.

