### Randomization

Participants will undergo three pairs of treatment with melatonin and placebo. In each pair, the order of treatment will be randomized. In particular, the first period for each patient will be randomized in variable block sizes of 4 and 6, stratified by age (<12 and ≥ 12 years) and country (Canada or Australia), to ensure a balance of the treatment groups for the parallel-group RCT. The randomization code will be developed by the study statistician. The randomization code will be provided to the central research pharmacy for each participating site and to maintain the blind. When a participant has been enrolled, the research pharmacy will randomize the subject based on the master randomization list and courier six bottles numbered 1–6, corresponding to each week’s treatment. Each bottle will contain seven capsules (or 14 for children who weigh < 40 kg) to be taken over 7 days. Randomization codes will be kept by the research pharmacy in case the code needs to be broken for safety reasons as determined by the Data Safety and Monitoring Board (DSMB).

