#### Aggregated analysis

N-of-1 trials will be combined using a multilevel random effects model that incorporates variance within and between patients. This within-patient level will incorporate variation resulting from the treatment crossovers as well as time effects modeled in various forms (e.g., linear trends, nonlinear trends, and carryover effects). Each within-patient regression coefficient will be treated as a random effect that can vary based on these between-patient factors. The primary analysis will calculate the average treatment effect (i.e., will model the mean of the individual treatment effects as a constant). Secondary analyses will model the mean as a function of factors that vary among patients such as age, sex, and dose. These terms describe the main effects of these factors, their interactions with the treatment, and their interaction with time. A full list of the factors evaluated for these subgroup analyses is given below.

The full multilevel model will return estimates of both average effects across the population of patients, as well as effects for individuals informed by the results on other participants. The predicted effects for an individual are weighted averages of the individual’s data and the averages from others. This model incorporates correlations among the measurements within an individual. It also enables comparison of the individual’s predicted treatment effect using the multilevel model with that from using only that individual’s data.

Carryover, the phenomenon whereby the effects of one treatment may continue to affect the outcomes measured after the next treatment is started, is always a risk in crossover studies. It is not expected that placebo effects would carry over into a melatonin period, but melatonin effects may carry over into a placebo period. Carryover might also differentially affect measurements made in a melatonin treatment period that follows another melatonin treatment period. We will investigate various adjustments for carryover, such as discarding the first measurements in a treatment period on outcomes measured daily, to determine whether results are sensitive to carryover. These adjustments will allow for potential differential carryover by treatment regimen.

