#### Subgroup analyses

Primary subgroup analyses include the two main stratification factors: (1) age (<12, ≥ 12 years) and (2) country (Australia and Canada). Exploratory analyses will look at (3) the type of stimulant, (4) weight-adjusted dose of stimulant, (5) presence of psychiatric comorbid illness, (6) gender, (7) calendar time of enrollment as a proxy for differences by climactic season, (8) severity of SOL, and (9) referring physician/clinic.

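### Apart from baseline SOL, the first-period RCT covariates are to be chosen by observed baseline imbalance; this omits the age and country strata and costs precision, without biasing the result

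*Protocol article*

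**What the plan says.** Four places in the protocol article bear on the covariates of the first-period RCT comparison.

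- **Statistical analysis plan** (general paragraph): "Regression adjustments will be carried out for variables found to be unbalanced at baseline between treatment and placebo groups". The sentence is not labelled as a sensitivity analysis. It contrasts a treatment group with a placebo group, so in practice it concerns the first-period comparison; in the N-of-1 series each child receives both.
- **Parallel-group RCT analysis**: the comparison is made "for all outcomes adjusted for the average baseline SOL determined by the pre-randomization sleep-hygiene phase". This is the only covariate fixed in advance.
- **Randomization**: the first period is randomised in blocks of 4 and 6, stratified by age (cut at 12 years) and by country, "to ensure a balance of the treatment groups for the parallel-group RCT".
- **Subgroup analyses**: "Primary subgroup analyses include the two main stratification factors". Age also appears under Aggregated analysis: "Secondary analyses will model the mean as a function of factors that vary among patients such as age, sex, and dose". Neither place puts age or country into the main RCT model.

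**The concern.** A baseline difference between correctly randomised groups says nothing about whether the variable predicts the outcome. Choosing covariates by imbalance therefore leaves the model unknown until the baseline table is seen, and it can pass over strong predictors that happen to be balanced.

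The rule also works against the stratification. Stratified blocks reduce the real variability of the treatment difference, but a model without the strata does not credit that reduction, so its interval is wider than it need be. Because the blocks hold age and country close to balance, the rule will almost never bring them in.

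A third, smaller matter is that baseline SOL is the named covariate for outcomes such as night-time awakenings, the Conners' 3, and child and parent quality of life, to which it may be only weakly related.

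What is at stake is the precision and predictability of the RCT estimate. The second primary objective sets that estimate beside the aggregated N-of-1 estimate, so avoidable width on the RCT side makes it a poorer comparator.

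**Working it through.** **1. The plan's own figure.** Inputs from Sample size: difference 22.5 min, SD 60 min, two-sided 0.05, power 90%.

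n per group = 2 × (1.960 + 1.282)² × 60² / 22.5² ≈ 149.4, rounded up to 150. Power at 150 per group is 0.901. The stated 150 reproduces. The formula takes no credit for any covariate, so the adjustment rule does not affect it.

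**2. What the stated rules admit to the RCT model.** Baseline SOL always enters. Other variables enter only if found unbalanced. Age group and country are balanced by the stratified blocks, so they stay out.

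**3. How often chance would shape the model.** The article gives no definition of unbalanced. Assume, for illustration, a significance screen of k independent baseline variables: P(at least one flagged) = 1 − (1 − threshold)^k.

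| k | threshold 0.05 | threshold 0.10 |
|---|---|---|
| 5 | 0.226 | 0.410 |
| 8 | 0.337 | 0.570 |
| 10 | 0.401 | 0.651 |

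**4. Does the rule harm the test?** Simulation with 150 per arm, one candidate covariate, least-squares regression and a two-sided 0.05 test (8,000 runs under no effect, 4,000 with a 22.5-min effect). The covariate–outcome correlation is assumed.

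| Correlation | Type I error, imbalance rule | Power, imbalance rule | Power, prespecified |
|---|---|---|---|
| 0.3 | 0.052 | 0.905 | 0.919 |
| 0.5 | 0.041 | 0.906 | 0.962 |
| 0.7 | 0.037 | 0.912 | 0.997 |

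The Monte Carlo standard error at 0.05 is √(0.05 × 0.95 / 8000) ≈ 0.0024, so 0.052 is compatible with 0.05. The rule does not inflate type I error. It turns conservative as the covariate becomes more prognostic, and it gives up most of the power that prespecified adjustment would add.

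**5. Leaving out the strata.** Let R² be the share of the SOL variance remaining after baseline SOL that age group and country explain (assumed). The reported standard error is too wide by 1/√(1 − R²). The last two columns come from a simulation of four near-equal strata without baseline SOL in the model; there R² is simply the share of the modelled variance.

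| R² | SE factor | Type I error, strata ignored | Power, ignored → included |
|---|---|---|---|
| 0.05 | 1.026 | 0.046 | 0.909 → 0.914 |
| 0.10 | 1.054 | 0.037 | 0.909 → 0.923 |
| 0.20 | 1.118 | 0.028 | 0.929 → 0.958 |

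With the strata included, type I error was about 0.05 throughout. At R² = 0.10 the reported standard error is what 300 × (1 − 0.10) = 270 children would give with the strata in the model.

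These simulations are frequentist. The primary analysis is Bayesian with noninformative priors, for which the results should be close.

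**6. Secondary outcomes.** For diary SOL, baseline SOL is the outcome's own baseline. For the other outcomes listed under Secondary outcomes, the article names no baseline value as covariate except SOL, and it does not say which of them are measured before randomisation.

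**The case against.** The strongest reply has four parts.

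- **The main covariate is already fixed.** Baseline SOL is prespecified and is correct for the primary outcome. This stands. A reader might infer that every outcome, the primary included, is adjusted for the wrong baseline; the text does not support that.
- **The rule is harmless to validity.** It looks at baseline data, not outcomes, and the statistician is blinded. This also stands. A reader might infer bias or a raised false-positive rate; the simulations show neither.
- **The strata may be in an analysis plan that is not shown.** They are not ignored by the trial: they are the primary subgroup factors, and age enters secondary aggregated models. A condensed article need not list every covariate, and the missing threshold and candidate list are not the complaint. But the article does state how covariates beyond baseline SOL are chosen, and balanced strata cannot enter that way. A later plan that prespecified them would have to override the stated rule.
- **The sizes are assumed.** This is correct. The article gives no number of baseline variables, no imbalance test and no variance explained. If age and country act mainly through baseline SOL, the gain from including them could be close to nothing.

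The aggregated N-of-1 analysis compares treatments largely within each child and is little affected.

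**Conclusion.** The point holds as a matter of efficiency and of fixing the model in advance. Apart from baseline SOL, chance imbalance decides the covariates of the first-period RCT model, and the two stratification factors lie outside the stated adjustment set. The consequence is lost precision and conservative intervals: a standard error about 2.6%, 5.4% or 11.8% too wide if the strata explain 5%, 10% or 20% of the SOL variance left after baseline SOL. Those shares are assumptions, and the 23% to 40% chance of a flag at a 0.05 threshold rests on an assumed screen of 5 to 10 independent variables.

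A reader might conclude that the trial is underpowered. It is not on this account: 150 per group gives 90% power without any covariate. For secondary outcomes the covariate is probably weaker than it could be, but whether a better one exists depends on what is collected before randomisation.

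**What to change.** Replace the imbalance sentence with a prespecified first-period RCT model:

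- treatment, age stratum and country for every outcome;
- baseline SOL for the SOL outcomes;
- for each secondary outcome, its own pre-randomisation value where one is collected, and otherwise baseline SOL as now.

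Keep any adjustment for observed imbalance only as a labelled sensitivity analysis.

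For the strata and baseline SOL this is a change of wording, since both are already recorded. For the secondary outcomes, first confirm which have a pre-randomisation value. The fallback to baseline SOL means that no new data collection is required. The sample size does not change.
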